
**Fig. 5 Fig5:**
[figure not shown]
Walking adaptability assessment using the 10 Meter Walking Test with context: (**a**) obstacle avoidance; (**b**) targeted stepping and; (**c**) tandem walking

**Fig. 6 Fig6:**
[figure not shown]
Walking adaptability assessments using the Interactive Walkway: (**a**) avoidance of suddenly appearing obstacles and (**b**) walking to a sequence of stepping targets, both presented on the walking surface in a gait-dependent manner

Secondary outcome measures are drawn from a comprehensive set of common clinical measures to determine walking ability, balance, and other walking-related constructs, including Timed Up-and-Go test [38] and Functional Ambulation Category [23]. The obstacle-avoidance subtask of the modified Emory Functional Ambulation Profile will be performed [39], a conventional clinical test closely related to the construct of walking adaptability. The modified Emory Functional Ambulation Profile is reliable and valid for use in people with stroke [40]. Balance will be assessed using the Berg Balance Scale, which provides a psychometrically sound measure of balance impairment for use in post-stroke assessment [40, 41]. Executive function will be assessed using the valid and reliable Trail Making Test [42]. Balance confidence will be assessed with the Activities-specific Balance Confidence scale, a questionnaire measuring balance confidence in performing specific activities, which has good test-retest reliability and validity [43, 44]. Self-reported limitations in walking will be assessed using the Walking Questionnaire [45], which targets experienced limitations in indoor and outdoor walking relative to pre-stroke walking limitations. Finally, the Nottingham Extended Activities of Daily Living scale [46–48] will be used to assess activities of daily living. Table 3 provides an overview of the tests that will be performed at T0, T1, T2 and T3.

**Table 3 Tab3:** Overview of all tests performed at T0, T1, T2 and T3

Primary outcome measure
10 Meter Walking Test (m/s)
Secondary outcome measures
10 Meter Walking Test with context (m/s, number of errors)
10 Meter Walking Test with a cognitive dual-task (m/s, DTP)
10 Meter Walking Test with context and a cognitive dual-task (m/s, number of errors, DTP)
Interactive Walkway targeted-stepping assessment (m/s, number of errors)
Interactive Walkway obstacle-avoidance assessment (m/s, number of errors)
Interactive Walkway obstacle-avoidance assessment with a cognitive dual-task (m/s, number of errors, DTP)
Timed Up-and-Go test (m/s)
Functional Ambulation Category (3–5)
Obstacle-avoidance subtask of the modified Emory Functional Ambulation Profile (m/s)
Berg Balance Scale (0–56)
Activities-specific Balance Confidence scale (0–100 %)
Trail Making Test (s)
Walking Questionnaire
Nottingham Extended Activities of Daily Living scale (0–66)

Finally, the number of steps taken per therapy session will be recorded, since we expect that the amount of walking practice per session (defined as the number of steps performed during therapy sessions) will be higher for treadmill-based C-Mill therapy than for the overground FALLS program. This expectation will be tested by comparing this process measure between the two intervention groups.

### Sample size

The primary outcome measure in this study will be walking speed. Previous clinical trials in people with stroke by Yang et al. [49] and Jaffe et al. [50] showed greater improvements in walking speed after treadmill training in a complex and challenging virtual reality environment than after, respectively, conventional treadmill training and overground obstacle-avoidance training [49, 50]. Unfortunately, effect sizes and required sample sizes for a controlled clinical trial with multiple comparisons cannot be estimated from the results of these studies, but both reported significant between-group differences in walking speed with small sample sizes of 9 to 10 participants in each intervention group. The study of Yang et al. [49] allows for a sample size calculation for post-hoc analyses for significant group effects on walking speed with independent *t* tests. Based on those results, we aim for a relative, clinically relevant, improvement in walking speed of 0.50 km/h (*∆*) with a common standard deviation (*SD*) of 0.47 km/h, which results in a sample size of 14 participants in each group to achieve 80 % power with a two-tailed *α* of 0.05, i.e., following$$ N=\frac{2S{D}^2{\left({Z}_{\alpha }+{Z}_{\beta}\right)}^2}{\varDelta^2} $$[51]. Considering a drop out of 10–25 %, we chose to increase our sample to 20 participants in each intervention group to be on the safe side for establishing the relative efficacy of the two interventions in terms of improvements in walking speed.

### Data analysis

Descriptive group statistics will be used to characterize the two intervention groups in terms of sex, age, height, body mass, Mini-Mental State Examination, Functional Ambulation Category, medication use, co-morbidities, side and location of the lesion, current living situation, daily functioning and the use of assistive devices, as well as perceived discomforts during and after therapy sessions and participant’s experience with the therapy. An independent *t* test will be used to compare the mean number of steps taken per session between the two interventions.

Primary and secondary longitudinal outcome measures that are normally distributed will be analyzed using repeated-measures ANOVA with the between-subject factor group (two levels: C-Mill therapy and the FALLS program) and the within-subject factor time (four levels: pre-intervention [T0], post-intervention [T1], retention [T2], and follow-up [T3] tests). Post-hoc analysis using independent *t* tests between groups per time level will be performed in case of significant interaction effects. For ordinal or non-normal distributed variables, we will use Mann–Whitney *U* tests and Friedman tests to evaluate possible main effects of group and time, respectively. To analyze possible interactions between groups and times, we will apply Kruskal–Wallis tests to change scores (i.e., relative to the previous time level) at T1, T2, and T3. When significant, Mann–Whitney *U* post-hoc tests will be performed to identify between-group differences in change scores per time level. Significant effects are assumed for *P* < 0.05. Data will be analyzed as randomized. Missing data will be imputed using the data from the last available measurement.

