Besides task-specific and context-specific training, other key ingredients for effective rehabilitation include variability in practice, feedback of performance, and amount of movement practice [6–8, 16, 17]. Both interventions comprise variability in practice, given their wide variety of tasks and exercises. Moreover, both interventions allow for performance feedback, either by group discussions and direct feedback provided by therapists (FALLS program) or by direct feedback of walking adaptability exercise performance, e.g., visual feedback with regard to obstacle hits (C-Mill therapy). However, treadmill-based C-Mill therapy probably allows for a greater amount of walking practice (defined as the number of steps taken per session), because it incorporates treadmill walking, which has been suggested to elicit more steps per session than overground training [18–22]. In this study, we will empirically test this suggestion, using the amount of walking practice as a process measure.

The study’s aim is to compare the effects of two promising interventions for improving walking speed, walking adaptability, and commonly used clinical measures of walking and balance in persons after stroke: treadmill-based C-Mill therapy [14, 15] and the overground FALLS program [9]. We expect that C-Mill therapy will result in better outcomes than the FALLS program because of the expected greater amount of walking practice per session of equal duration.

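### No single deciding test is fixed for walking speed: no visit or contrast is named, and a normality judgment switches the primary analysis between two batteries that answer different questions

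*Protocol article*

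**What the plan says.** The Sample size section states "The primary outcome measure in this study will be walking speed", and the Background gives the hypothesis: "We expect that C-Mill therapy will result in better outcomes than the FALLS program". Neither names a visit.

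The Data analysis section sets out two routes for the primary outcome:

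- **If normally distributed:** "Primary and secondary longitudinal outcome measures that are normally distributed will be analyzed using repeated-measures ANOVA", with "the within-subject factor time (four levels: pre-intervention [T0], post-intervention [T1], retention [T2], and follow-up [T3] tests"). Then: "Post-hoc analysis using independent *t* tests between groups per time level will be performed in case of significant interaction effects".
- **Otherwise:** "For ordinal or non-normal distributed variables, we will use Mann–Whitney *U* tests and Friedman tests to evaluate possible main effects of group and time, respectively". The interaction is examined by Kruskal–Wallis tests on change from the preceding visit, at T1, T2 and T3, with Mann–Whitney tests to follow where significant.

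The threshold is 0.05 throughout and no adjustment is stated. Missing values are filled with the last available measurement.

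The Sample size section powers a post-hoc independent t test on walking speed, visit unnamed. It says that effect sizes and sample sizes "for a controlled clinical trial with multiple comparisons cannot be estimated from the results of these studies".

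**The concern.** A reader of the results should be able to say beforehand which P value decides whether C-Mill beats FALLS on walking speed. The text does not allow that. In the ANOVA branch, the candidates are the group effect, the interaction and a t test at any of T1, T2 or T3. In the rank branch, they are the group test and three change-score tests. The distribution of the outcome decides which set applies.

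The sets also measure different things. One compares speed at a visit; the other compares change since the previous visit. A benefit gained by T1 and fully kept is a difference at T2 in the first and zero change at T2 in the second.

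The per-visit t tests use raw speed, although T0 is measured on everyone and the sample size is framed as an improvement. Between-person spread that T0 could remove stays in the error term.

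**Working it through.** **The plan's own figure.** Inputs from Sample size: difference 0.50 km/h, SD 0.47 km/h, two-sided 0.05, 80% power.

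N = 2 × 0.47² × (1.960 + 0.842)² / 0.50² = 0.4418 × 7.849 / 0.25 = 13.87, so 14 per arm.

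Dropout: 14/0.90 = 15.6 (16) and 14/0.75 = 18.7 (19), so 20 per arm is consistent. On these inputs one such test has power 0.92 with 20 per arm and 0.83 with 15. The arithmetic is right; which visit it powers is not stated.

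**Assumptions added.** The protocol gives no between-visit correlation. The simulations use 20 per arm, four visits and normal data. The correlation is 0.8 between all visits unless stated; 0.5 to 0.9, and correlations that decay with time, were also tried.

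The protocol does not say whether 0.47 km/h is the SD of speed or of change, so both readings are carried:

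- SD of speed: effect = 0.50/0.47 = 1.06 SD.
- SD of change: SD of speed = 0.47/√(2 × (1 − 0.8)) = 0.743 km/h, so effect = 0.50/0.743 = 0.67 SD.

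**1. No effect at any visit**

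| Claim counted as success | Rate |
|---|---|
| ANOVA branch: interaction plus at least one post-baseline t test | about 1%; up to about 2.5% over the correlations tried |
| ANOVA branch: interaction or group main effect | about 10% (9 to 11% over the compound-symmetry and AR(1) correlations) |
| Rank branch: at least one of three change-score tests | about 13 to 14% |
| Rank branch: the same, or the group test | 17 to 18% |

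With two groups, the Kruskal–Wallis test and the Mann–Whitney test (normal approximation, no continuity correction) give the same P value. The follow-up test therefore repeats the first and gates nothing.

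**2. True effect at T1 only**

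| T1 effect | Interaction significant | False difference at T2 or T3 |
|---|---|---|
| 0.67 SD | about 93 to 94% | about 7 to 8% |
| 1.06 SD | about 100% | about 8% |

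Once the interaction is significant because of T1, it no longer protects the later visits.

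**3. Benefit of 1.06 SD reached at T1 and held to T3.** The gated t tests find a difference at T2 or T3 in about 95% of trials. The change-score tests at T2 and T3 each reject in about 5%, the null rate. The T1 change-score test still detects the gain, so what depends on the normality judgment is whether persistence can be shown.

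**4. Power at T1**

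| T1 effect | Gated raw t test | T1 difference adjusted for T0 (ANCOVA) |
|---|---|---|
| 0.67 SD | about 52% | about 92% |
| 1.06 SD | about 91% | close to 100% |

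Adjusting for T0 reduces the SD by √(1 − 0.8²) = 0.6, so 0.67 SD becomes 0.67/0.6 = 1.12 residual SDs.

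**The case against.** The strongest defence is that the interaction gate is a real safeguard. A reader might infer from four unadjusted t tests that the ANOVA branch inflates the false-positive rate to 14 to 19%. It does not: if nothing differs at any visit, a false visit-level claim occurs in well under 5% of trials. The 8% for T2 or T3 arises only when T1 truly differs. It is then mainly a risk of misplacing when the effect occurs, since a false T2 or T3 result without a significant T1 result occurs in about 3 to 4% of runs.

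Several other stronger readings also fail:

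- **The powered test is not wholly undefined.** The Sample size section names an independent t test, two-tailed; the visit is what is missing. It also says openly that a design with multiple comparisons could not be sized.
- **The branching is a rule set in advance**, not an improvised choice. How normality is judged may be in the analysis plan. What stands is that the two routes have different estimands.
- **The ANOVA group effect is not declared proof of efficacy.** The 10% applies only if it is used that way, which the text does not rule out.
- **Lack of a sphericity correction is no finding.** An article commonly leaves that to the analysis plan.
- **A T0 difference cannot be put down to chance alone.** The Study design section has participants told their allocation before the T0 tests and leaves the assessor unblinded, so knowledge of allocation could also contribute.

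The missing visit and contrast, the switch of estimand, the ungated rank branch and the unused baseline all survive this defence.

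**Conclusion.** The point holds as a matter of what the Data analysis section fixes. Walking speed has no single deciding test, and a normality judgment selects between two estimands. This is not a general failure of error control in the ANOVA branch. Control is lost in the rank branch, if the group main effect counts as success, or at T2 and T3 once T1 differs. The loss of power from ignoring T0 is the larger practical cost on the change-SD reading (about 52% against 92%). It is smaller if 0.47 km/h is the SD of speed itself (about 91% against nearly 100%). The rates for T2 and T3 and the power figures depend on the assumed correlation and effect size. The absence of a named visit and the change of estimand do not. The change should be made, and the planned 20 per arm need not increase.

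**What to change.** Name one visit in advance, for example T1, the assessment immediately after the intervention. The documents do not themselves single out T1, so the investigators must choose. Make the C-Mill minus FALLS difference in 10 Meter Walking Test speed at that visit, adjusted for T0, the sole primary test at two-sided 0.05. Use it whatever a normality check shows, with a permutation or bootstrap analysis as sensitivity. Report the other visits as secondary, and do not use the T0 t test or the group main effect as evidence of efficacy. Because T0 is measured after allocation is known, say so when presenting the adjusted result.

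ANCOVA is enough. If a mixed model is preferred, state that it replaces last-observation imputation for this outcome; that changes the missing-data method and is more than wording.

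The cost is that the other visits can no longer stand alone as proof of superiority. Keeping all three post-baseline visits claimable with a Bonferroni correction (0.05/3) would need 19 evaluable per arm on the plan's inputs, or 19/0.75 = 25.3, so 26 per arm with 25% dropout. The planned 20 would not cover that.

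### The trial is sized on a difference in improvement, but its follow-up t tests compare unadjusted walking speed at each visit, so the stated 80% power need not apply to them

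*Protocol article*

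**What the plan says.** The Sample size section identifies the test that it is meant to power: one earlier trial "allows for a sample size calculation for post-hoc analyses for significant group effects on walking speed with independent" t tests. It gives the target as "we aim for a relative, clinically relevant, improvement in walking speed of 0.50 km/h", paired with an SD "of 0.47 km/h, which results in a sample size of 14 participants in each group", for "80 % power with a two-tailed *α* of 0.05". It then allows for dropout: "we chose to increase our sample to 20 participants in each intervention group". The section closes by describing the aim in terms of improvement in speed.

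The Data analysis section starts with a repeated-measures ANOVA with group as one factor and time as the other, T0 being one of the four time levels. For normally distributed outcomes the follow-up is then fixed: independent t "tests between groups per time level will be performed in case of significant interaction effects". Neither a change score nor a T0 covariate is named. For ordinal or non-normal outcomes the same section does test change scores, each taken against the previous time level. Missing values are filled with the last available measurement.

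**The concern.** The two sections describe different quantities. A difference in improvement is judged against the spread of change within people. A difference in speed at one visit is judged against the spread of speed between people. When speed before and after treatment is well correlated, the second spread is the larger, and the same 0.50 km/h advantage becomes harder to detect.

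These t tests are the only ones for which the article claims 80% power. The hypothesis is directional (C-Mill better), and a four-level interaction test gives neither direction nor timing; the per-visit tests are the named step that supplies both. A real advantage could thus produce a significant interaction with no significant difference at any visit, which would be hard to interpret. A chance difference in T0 speed would also pass uncorrected into the T1, T2 and T3 comparisons. Minimization uses time after stroke, age and Functional Ambulation Category, but not walking speed.

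**Working it through.** **Inputs from the article.** Difference 0.50 km/h; SD 0.47 km/h; two-sided alpha 0.05; power 80%; 20 per arm. Last-value imputation keeps up to 20 per arm in the analysis, so 20 is the n used here.

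**Assumed, because the article does not give it.** The correlation r between T0 speed and later speed, shown over a range, with equal variance at both visits.

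**1. The article's own figure.** 2 × 0.47² × (1.960 + 0.842)² / 0.50² = 13.87, rounded up to 14 per group. It reproduces. With the exact noncentral t, power on this scale is 77% at 14 per group and 91% at 20.

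**2. From the SD of change to the SD of speed.** If 0.47 is the SD of change, then 0.47² = 2 × SD_raw² × (1 − r), so SD_raw = 0.47 / √(2(1 − r)). At r = 0.8: 0.47 / √0.4 = 0.743 km/h.

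**3. Power at 20 per arm (exact noncentral t).** The noncentrality is 0.50 / (SD × √(2/20)). The raw test uses SD_raw. The T0-adjusted test uses SD_raw × √(1 − r²).

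| r | SD_raw (km/h) | Power, raw speed | n per arm for 80%, raw | Adjusted SD (km/h) | Power, T0-adjusted |
|---|---|---|---|---|---|
| 0.5 | 0.47 | 91% | 15 | 0.41 | 97% |
| 0.7 | 0.61 | 72% | 25 | 0.43 | 94% |
| 0.8 | 0.74 | 54% | 36 | 0.45 | 93% |
| 0.9 | 1.05 | 31% | 71 | 0.46 | 92% |

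A t test on change from T0 keeps SD 0.47 and so has 91% at every r.

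**4. Break-even.** With 20 per arm the raw test falls below 80% once SD_raw exceeds 0.55 km/h (0.55 / 3.6 = 0.153 m/s). The matching correlation is 1 − 0.47² / (2 × 0.55²) = 0.635, or about 0.64.

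**5. The other reading.** If 0.47 is already the SD of speed at a visit, the raw test has 91% at 20 per arm.

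**6. The interaction.** In a simulation (10,000 trials per setting, equal correlation between all visits, 20 per arm), the group-by-time test had about 94% power for a sustained 0.50 km/h effect and about 91–92% for a fading one, at every r tried from 0.5 to 0.95. Requiring both a significant interaction and a significant T1 t test on raw speed gave 85%, 69%, 51% and 30% at r = 0.5, 0.7, 0.8 and 0.9 (sustained effect).

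**7. Chance T0 imbalance.** The standard error of the T0 difference is SD_raw × √(2/20): 0.19, 0.24 and 0.33 km/h at r = 0.7, 0.8 and 0.9, against a target of 0.50 km/h. This ignores any balance gained through the minimization factors.

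**The case against.** The strongest reply is that the loss depends on a number the article does not contain. It gives no SD of walking speed at a visit and no correlation, and it never says outright that 0.47 km/h is an SD of change. This stands. At r = 0.5, or if 0.47 is the SD of speed, there is no shortfall at 20 per arm; at r = 0.7 it is modest. One might answer that 0.47 km/h is too narrow for a between-person SD in patients at Functional Ambulation Category 3 to 5. The article gives no walking speeds for such patients, so that argument cannot settle the matter. What favours the change reading is that the SD is paired with an improvement.

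Second, the interaction comes first and rests on within-person change. Stable differences between people, T0 imbalance included, cancel out of it. Whether the therapies differ in improvement is therefore tested on a suitable scale, with good power in the simulation. This stands too, and it limits the point to the follow-up tests.

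Third, a reader might take the lower dropout bound (20 less 25% = 15 per arm) and quote lower power still. That would be a completer analysis, which is not planned. Carrying values forward may dilute the effect, but that is a separate matter.

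Fourth, the t tests cover T0 as well, so an imbalance would be visible. It would still not be adjusted for.

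None of this removes the mismatch between the two sections, or between the change scores of the non-normal branch and the raw speed of the normal one.

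**Conclusion.** The point holds in a conditional form. The sample size concerns a difference in improvement; the follow-up t tests, as written for normal outcomes, compare unadjusted speed. The 80% therefore need not describe those tests. If 0.47 km/h is the SD of change, variances are equal across visits and 20 per arm are analysed, power is about 91%, 72%, 54% or 31% for r of 0.5, 0.7, 0.8 or 0.9, against 92–97% with T0 adjustment.

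A reader might infer that the trial as a whole has far less than 80% power. The documents do not support that: the shortfall needs r above about 0.64 and becomes large only from about 0.8, and the interaction test is unaffected. What is at risk is the ability to say which group is better and at which visit. Whatever the true r, adjusting for a T0 speed that is already measured gains precision if the correlation is positive.

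**What to change.** 1. In Data analysis, replace the follow-up t tests on raw walking speed with between-group comparisons at T1, T2 and T3 that take T0 speed as covariate: an ANCOVA per visit, or one mixed model with T1 to T3 as responses, T0 speed as covariate and a group-by-time term. At minimum, test change from T0, which alone would match the sample-size calculation.
2. In Sample size, state whether 0.47 km/h is the SD of change or of speed at a visit, and that the 80% power refers to the change-from-T0 or baseline-adjusted contrast.
3. Bring the non-normal branch into line. Its change scores are taken against the previous visit, so only the T1 score is a change from T0.

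The cost is a few sentences. No new data and no more participants are needed. The article reports recruitment as ongoing, so the change should be made before outcomes are compared between the groups.

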### Study design

The proposed study is a single-center, parallel group randomized controlled trial with pre-intervention, post-intervention, retention, and follow-up tests to determine the relative efficacy of the interventions: treadmill-based C-Mill therapy and the overground FALLS program. After giving informed consent, participants will be randomly assigned to one of the two interventions using an automated, custom-made minimization algorithm written in MATLAB. The minimization procedure is based on time after stroke, age and Functional Ambulation Category score to balance groups for these stratification factors. The research assistant will enter the data for randomization in the algorithm and the participant will subsequently be informed about the resulting group allocation before the pre-intervention tests. Subsequently, the assessor will schedule the participants for the assigned 5 week intervention program. Pre-intervention tests (T0) to characterize groups and obtain baseline values of primary and secondary outcome measures will be performed one week prior to the intervention program. Within one week after completing the intervention, post-intervention tests (T1) will be performed. The same tests will be conducted 5 weeks (retention tests, T2) and 12 months (follow-up tests, T3) after completing the intervention. All assessments will be performed at the rehabilitation center. Because of the nature of the intervention studied, therapists and participants cannot be blinded to group allocation. The assessor will also not be blinded to group allocation, because of pragmatic constraints related to the planning of assessments and therapy sessions. Figure 2 shows a flow chart of the procedures that participants will undergo at T0, T1, T2 and T3.

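### For ordinal or non-normal outcomes, the interaction test uses change from the previous visit, so it does not show whether a between-group benefit is retained at 5 weeks or 12 months

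*Protocol article*

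**What the plan says.** The Data analysis section has two branches.

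- **Normally distributed outcomes.** Repeated-measures ANOVA with "between-subject factor group (two levels: C-Mill therapy and the FALLS program") and "within-subject factor time (four levels: pre-intervention [T0], post-intervention [T1], retention [T2], and follow-up [T3] tests"). If the interaction is significant, independent t "tests between groups per time level will be performed in case of significant interaction effects". These compare the scores at each visit.
- **Ordinal or non-normal outcomes.** The branch opens "For ordinal or non-normal distributed variables, we will use Mann–Whitney" U tests for a main effect of group and Friedman tests for a main effect of time. For the interaction, the article states "we will apply Kruskal–Wallis tests to change scores (i.e., relative to the previous time level) at T1, T2, and T3". It continues: "When significant, Mann–Whitney *U* post-hoc tests will be performed to identify between-group differences in change scores per time level".

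The Study design section gives the meaning of the later visits: "The same tests will be conducted 5 weeks (retention tests, T2) and 12 months (follow-up tests, T3) after completing the intervention".

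The significance level is 0.05 for each test, and missing values are filled with the last available measurement.

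**The concern.** The names retention test and follow-up test pose a plain question: does a between-group difference in gain over baseline still exist 5 weeks and 12 months after therapy? T2−T1 and T3−T2 do not answer it. If both arms keep what they gained, both contrasts are zero however large the retained advantage is. If an advantage builds slowly, each contrast sees only a part of it. The non-parametric branch states no between-group test of change from T0 at T2 or T3.

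The ANOVA branch compares levels per visit, so the outcome of a normality check changes which question is asked at T2 and T3 for outcomes in the same table.

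A second, smaller matter is that testing by Kruskal–Wallis and then by Mann–Whitney looks like a two-stage procedure. With two groups it is one test run twice.

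**Working it through.** **Inputs from the article.** Difference 0.50 km/h, SD 0.47 km/h, two-sided 0.05, 80% power, 20 per group and dropout 10–25% (Sample size); two groups and four visits (Data analysis).

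**The plan's own figure.** N = 2·SD²·(Zα+Zβ)²/Δ² = 2 × 0.47² × (1.960+0.842)² / 0.50² = 13.87, so 14 per group, as stated. Allowing for dropout, 14/0.90 gives 16 and 14/0.75 gives 19, so 20 covers the range. The sample size is sound and this point does not touch it.

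**What the contrasts target.** Write the true between-group differences at T1, T2 and T3, with no difference at T0.

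- Lasting benefit (0.50, 0.50, 0.50): successive contrasts 0.50, 0, 0; from T0: 0.50, 0.50, 0.50.
- Benefit gone by T3 (0.50, 0.50, 0): successive 0.50, 0, −0.50; from T0: 0.50, 0.50, 0.
- Gradual gain (0.17, 0.33, 0.50): successive 0.17, 0.16, 0.17; from T0: 0.17, 0.33, 0.50.

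**Simulation.** 20 per arm, 2,000 trials per scenario. Assumptions: normal data, 0.47 km/h taken as the SD of a change, equal correlation 0.8 between all visits. The SD at one visit is then 0.47/√(2×0.2) = 0.74 km/h. Entries are the percentage of trials significant at 0.05 for T1 / T2 / T3.

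| True pattern | Successive change (plan) | Change from T0 | Raw scores per visit |
|---|---|---|---|
| Lasting | 88 / 4 / 6 | 88 / 89 / 89 | 52 / 51 / 53 |
| Gone by T3 | 88 / 6 / 88 | 88 / 88 / 4 | 52 / 52 / 6 |
| Gradual | 19 / 16 / 19 | 19 / 54 / 88 | 10 / 29 / 52 |
| No effect | 5 / 6 / 5 | 5 / 5 / 5 | 5 / 6 / 5 |

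For the lasting and gone-by-T3 patterns, correlations of 0.5 and 0.9 leave the first two columns essentially unchanged. The raw-score column depends heavily on the correlation: for a lasting benefit it is about 90% per visit at 0.5 and 30% at 0.9. In the gone-by-T3 pattern the 88% at T3 points to the other arm. With 25% of T3 values carried forward from T2 it is about 70%.

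**The Kruskal–Wallis step.** With two groups, H equals the square of the Mann–Whitney z (normal approximation, no continuity correction). In 4,000 data sets, half of them tied, the largest difference in P was about 1×10⁻⁷, with no disagreement at 0.05. With continuity correction, 0.2% disagreed.

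**Error over three visits.** With no effect, at least one of the three successive-change tests was significant in 12.5% to 13.9% of trials. Three independent tests would give 1 − 0.95³ = 14.3%.

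**The other reading.** If one Kruskal–Wallis test over all six group-by-visit cells was meant, it treats repeated measurements on a person as independent. It is not an interaction test either: it rejected in 98.5% of trials when both arms gained equally at T1.

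**The case against.** Much of the case against a stronger claim stands.

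- **Scope.** The rule covers ordinal or non-normal variables. A reader might infer that the primary analysis is compromised. The article sends walking speed to ANOVA unless it is judged non-normal, and it ties the sample size to t tests.
- **Stated purpose.** The tests are offered for interaction. In terms of means, no difference in all three successive changes is the same null as no difference in all three changes from T0. A lasting benefit is still found, at T1. What is lost is a direct answer at T2 and T3, and power when the gain is gradual.
- **Another test exists.** A Mann–Whitney test for a group effect is planned separately, so it would be wrong to say that a lasting benefit cannot be found at all. That test ignores baseline, however, and the article does not say whether it is run per visit. It softens the problem without removing it.
- **Wrong sign.** A reader might infer that the plan declares the comparator superior at T3 when a benefit fades. It does not. The arms then truly differ in T3−T2 change, and the article speaks only of "post-hoc tests will be performed to identify between-group differences in change scores per time level". The result misleads only if read as an effect at T3.
- **Protection.** The article nowhere claims that the Kruskal–Wallis step controls error across visits. The redundancy is harmless in itself, and the 13% is ordinary unadjusted multiplicity.
- **Illustration.** The figures use normal walking-speed data, whereas this branch serves outcomes such as the Functional Ambulation Category, which is scored 3–5 and heavily tied. The percentages will not carry over to such outcomes; the zero contrasts for a retained benefit will.

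**Conclusion.** The point holds in this form: for outcomes on the non-parametric branch, the stated change tests describe when the arms diverge and do not test whether a between-group gain over baseline is retained at T2 or T3. This is a rule the article states, not a detail left to another document. It applies with certainty to the Functional Ambulation Category, probably to error counts and bounded scales such as the Berg Balance Scale, and to walking speed only conditionally.

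Under the assumptions above, detection of a lasting benefit falls from about 88% to about 5% at T2 and T3. Detection of a gradual gain at T3 is 18–19% instead of 88–89%. The two branches ask different questions at those visits. On the natural reading of one test per visit, the Kruskal–Wallis step is redundant; on the pooled reading it is invalid. The documents do not support reading this as a false claim of superiority, as a failure to detect any benefit, or as a flaw in the sample size.

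**What to change.** In the non-parametric branch:

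1. Define change scores relative to T0 at T1, T2 and T3. Successive changes may be kept as descriptive results.
2. Drop the Kruskal–Wallis step and run one Mann–Whitney test per visit on change from T0.
3. Holm-adjust the three tests within each outcome. Moving to T0 does not by itself control error over the visits.

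With arms alike at T0 on average, this branch and the ANOVA branch would then both address the between-group difference at a given visit, although one uses changes and the other levels.

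The cost is a few sentences and no data. Holm's strictest threshold is 0.05/3 = 0.0167. By normal approximation with 20 per arm, 0.50/(0.47 × √(2/20)) = 3.36. Power at one visit is then Φ(3.36 − 1.96) = 92% at 0.05 and Φ(3.36 − 2.39) = 83% at 0.0167. The second figure is the worst case, because Holm relaxes the threshold once a first test succeeds.

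Naming T1 as the single confirmatory visit, or using rank ANCOVA or a proportional-odds model with T0 as covariate, is optional and a matter of design preference.
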